### **10.6.2. Follow-up Requirements for Early Withdrawal**

If a participant has cause for premature withdrawal, or if the PI decides that the participant should withdraw, he or she will be asked to attend a Premature Withdrawal Visit. If this occurs before the 12-week post quit visit (final treatment visit), the Premature Withdrawal Visit will essentially mirror the 12-week post quit visit (if the subject is able). If the premature Withdrawal occurs after the 12-week visit, then the patient will simply be called on the phone for a final phone call assessment then withdrawn with payment for the encounters he/she was able to complete.

### **10.6.3. Replacement of Early Withdrawal(s)**

Sample size estimation from this trial is all based on intent-to-treat data and attrition is expected and included within the calculation of abstinence rates for all outcomes. As such, there will be no replacement for premature withdrawal of subjects or subjects lost to follow up.

## **10.7 Study Assessments**

### **10.7.1. Medical History**

Medical history assessments will be completed by each subject as part of standard clinical practice. A Clinical Trials Assistant or other Key Personnel will review this as part of the screening process. Appendix 1 provides an overview of medical history information to be collected and is considered a baseline measure.

### **10.7.2. Physical Exam**

A physical exam will be conducted as part of standard clinical practice by the Clinical Tobacco Treatment Specialist (TTS medical provider) at the initial visit to the TSCP or Duke CSC. Exam findings however, will not be used to exclude patients from participation in the study. The study only uses medications that are FDA approved for smoking cessation.

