**Contraindications:** The major contraindicated for bupropion are individuals with seizure disorder as bupropion is known to lower the threshold for seizures. Those undergoing acute discontinuation of alcohol and sedatives such as benzodiazepines should also not be prescribed for the same reason of increased seizure risk. It is also contraindicated in individuals with a diagnosis of bulimia or anorexia nervosa (GlaxoSmithKline, 2014). Individuals using Wellbutrin should not be prescribed additional bupropion. Bupropion should also not be started in individuals who have been taking Monoamine Oxidase inhibitors (MAOI) in the previous 14 days. It should also be avoided in those with hepatic impairment, pregnant women and if <18 years old (GlaxoSmithKline, 2014).

**Common Side effects:** The most commonly reported adverse reactions of bupropion (incidence  $\geq 5\%$  and  $\geq 1\%$  more than placebo rate) are: sleep disturbances, dry mouth, rhinitis, dizziness, anxiety, nausea, constipation, and arthralgia (GlaxoSmithKline, 2014).

Insomnia: 30 - 40%

Dry mouth: 10%

Constipation, pruritis and pharyngitis: <10%

Approximately 7-12% of individuals who report these adverse effects discontinue using bupropion, although some studies have reported 31 - 33% of individuals on a 300mg dose of bupropion discontinuing medications due to side effects and 25% of those on 150mg discontinuing medication due to side effects (J. R. Hughes, Stead, Hartmann-Boyce, Cahill, & Lancaster, 2014; Richmond & Zwar, 2003). Allergic reactions such as pruritus, hives, angioedema and shortness of breath have been described at a rate of 1-3 per thousand (J. R. Hughes et al., 2014; Richmond & Zwar, 2003).

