## 9 SUBJECT ELIGIBILITY

Patients who consent to participate in the study will be screened for the following inclusion/exclusion criteria.

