### **9.3 Exclusion Criteria (assessed study medical provider)**

7. Medical contraindication to the use of Varenicline or Nicotine Patch, or Bupropion (including seizure disorder)
8. Brain abnormality that would increase the patients risk for a seizure (including but not limited to a stroke or brain tumor)
9. Bulimia or anorexia
10. Currently undergoing discontinuation of alcohol or sedative (including benzodiazepines, barbiturates, or antiepileptic drugs)
11. Use of MAO-inhibitor (currently or in the last 14 days)
12. Taking Linezolid or intravenous methylene blue.
13. Significant adverse reaction to bupropion in the past
14. Symptomatic cognitive or emotive disorder such as untreated schizophrenia, severe untreated depression, anxiety.
15. Uncontrolled hypertension (systolic BP >160 mm Hg, diastolic BP >100 mm Hg) or hypotension
16. Chest pain in the last month (unless history indicates a non-cardiac source) or myocardial infarction in the past year
17. Unstable irregular heart rhythm
18. Symptomatic cardiac disorder
19. Moderate renal impairment or mild hepatic impairment (study provider discretion)
20. Current symptomatic lung disorder/disease (including but not limited to COPD, emphysema, and asthma) that requires oxygen
21. Migraine headache occurring more than once per week
22. Unexplained fainting spell within the last month
23. Uncontrolled diabetes (blood sugars >200 more than once per week, suffering from complications or on insulin)
24. Current cancer or treatment of cancer in the past 6 months (except basal or squamous cell skin cancer)
25. History of Tuberculosis or positive PPD
26. Suicidal ideating within the past 12 months or attempted suicide within the last 10 years.
27. Psychiatric hospitalization in the past 12 months
28. Red dye allergy
29. Any other major medical conditions (study provider discretion)

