## 10.1 Screening Examination

The screening examination will take place on the day of the screening visit. Subject data to be collected at the Screening Examination includes the following baseline measures: contact information questionnaire, demographics questionnaire, smoking-related medical history questionnaire, TSCP smoking history questionnaire, recent smoking history questionnaire, medication use and intolerance questionnaire, financial questionnaire, work break questionnaire, cost of smoking questionnaire, general health questionnaire, cancer questionnaire, self-efficacy questions, Fagerstrom Test for Nicotine Dependence (FTND), Mood and Physical Symptoms Scale (MPSS), Patient Health Questionnaire (PHQ-2 as well as PHQ-9 question 9), Generalized Anxiety Disorder-2 (GAD-2), Alcohol Use Disorders Identification Test (AUDIT-C), and the Perceived Stress Test (PSS-4). The subject will also complete a urine pregnancy test if female and of child-bearing potential.

The urine pregnancy test will be conducted by the CTA or other study staff with the appropriate training. Most information except the urine pregnancy test results will be documented in the EMR because these assessments are all part of standard clinical practice within the TSCP. If the screening visit occurs at the CSC, outside of the normal TSCP clinic, all information will be collected on paper forms or in REDCap. If the screening visit occurs at the TSCP during a routine clinic visit, the study Physician or Physician Assistant will review the visit documentation to assess eligibility. In the event of a screen failure, documentation of this will be noted in eResearch. Participants that fail the screening process will receive follow-up from the study physician to ensure the participant has been connected to appropriate clinical care.

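### Section 10.7.2 bars physical exam findings from excluding anyone, which contradicts the medical exclusions in Section 9.3 and the study clinician's eligibility review

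*Protocol*

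**What the plan says.** Section 10.7.2 places a physical exam by the tobacco treatment provider "at the initial visit to the TSCP or Duke CSC", as part of routine clinical care. It continues: "Exam findings however, will not be used to exclude patients from participation in the study". The sentence after that reads: "The study only uses medications that are FDA approved for smoking cessation".

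Section 9 opens with a general screening requirement: "Patients who consent to participate in the study will be screened for the following inclusion/exclusion criteria". Section 9.3 then gives criteria 7 to 29 to the study medical provider. They include criterion 17, "Unstable irregular heart rhythm", and criterion 15, "Uncontrolled hypertension (systolic BP >160 mm Hg, diastolic BP >100 mm Hg) or hypotension". Criterion 29 leaves other major conditions to the provider's discretion.

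On how eligibility is decided, Section 10.1 says that when screening happens at the TSCP during a routine clinic visit, "the study Physician or Physician Assistant will review the visit documentation to assess eligibility". The consent text in Section 10 is more general: it gives the study PA or MD access to the record so that the initial clinic visit can be reviewed for eligibility and safe inclusion.

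**The concern.** A provider who follows 10.7.2 to the letter cannot use what the exam shows to keep someone out. A provider who follows 9.3 must exclude anyone who meets a criterion, however the condition comes to light. For a condition that the participant has not reported and the chart does not record, but that the exam uncovers, the two instructions point in opposite directions.

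This happens at the gate to randomization. Medical exclusions protect participants and define the population studied, and here both could depend on which section a given provider happened to apply. The Section 10.6.1 provision for withdrawal by the PI does not close the gap, because it acts only after entry, and Section 10.6.3 says that withdrawn participants are not replaced.

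**Working it through.** No figure is stated and no arithmetic applies beyond a count, so the check is to set the sections side by side.

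1. *Is the 10.7.2 sentence limited anywhere?* No. It does not confine itself to findings outside the listed exclusions, and no other section narrows it.

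2. *Does the eligibility review cover the exam?* By reasonable inference, yes for TSCP patients. Section 10 says the TSCP provider's evaluation includes physical exams. The consent text has the study PA or MD review that initial visit for eligibility, and 10.1 repeats this for screening at a routine TSCP visit. For screening at the CSC, 10.1 says only that information goes on paper forms or into REDCap. Neither the 10.1 list of screening data nor the Schedule of Activities names a physical exam.

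3. *Which Section 9.3 criteria could an exam reveal?* There are 29 − 7 + 1 = 23 provider-assessed criteria. The protocol does not say how each is to be established, so this sorting is a judgement:

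| Criterion | Other sources in the protocol | Does the conflict bite? |
|---|---|---|
| 17, rhythm | Appendix 1 item on known rhythm problems | Yes, for a rhythm problem not already known |
| 29, other major conditions | None specified; source of information unrestricted | Yes; 10.7.2 imposes a limit that 29 does not have |
| 18, symptomatic cardiac disorder | Appendix 1 cardiac items | In part |
| 14, symptomatic cognitive or emotive disorder | Appendix 1 psychiatric items; PHQ-2 and GAD-2 at screening | In part |
| 15, blood pressure | Vitals, a separate line in the Schedule at the screening visit | No, if vitals are not counted as exam findings |
| 20, lung disease needing oxygen | Appendix 1 items on oxygen use and COPD | Hardly |

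Most of the remaining criteria (for example eating disorder, MAO-inhibitor use, past reaction to bupropion, dye allergy, psychiatric hospitalization) are matters of history or medication.

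4. *Does another provision settle it?* Section 10.1 invites only individuals who meet the criteria to the enrollment and randomization visit. That supports 9.3, but it does not say whether an exam finding may be used to judge that a criterion is met. The conflict therefore remains for 17 and 29, and in part for 14 and 18.

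**The case against.** The best defence is that 10.7.2 describes a routine clinical exam and means only that this exam is not an eligibility test in its own right. Section 9.3 still assigns the exclusions to the study medical provider, every consenting patient is screened, only those who meet the criteria go forward, and criterion 29 leaves wide discretion. A provider who knows of an excluding condition has several provisions to act on. This may well be what the sponsor intended, but the sentence does not say so, and a blanket rule should not depend on the reader supplying the limit.

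The objection does succeed against stronger readings that a reader might infer:

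- *That much of Section 9.3 becomes unenforceable.* The documents do not support this. Blood pressure has its own screening measurement, and criteria 14, 18 and 20 are largely captured by history or questionnaires.
- *That the approved-drug rationale is refuted by the contraindications in Section 5.2.* The leading example there is "The major contraindicated for bupropion are individuals with seizure disorder as bupropion is known to lower the threshold for seizures". Seizure disorder is established by history (Appendices 1 and 5), and criterion 7 already excludes it. A list of contraindications does not by itself contradict a statement about exam findings. Equally, drug approval does not narrow the 10.7.2 sentence, because Section 9.3 applies medical exclusions to these same drugs.
- *That the treatment comparison is biased.* Eligibility is settled before randomization, so an inconsistent exam rule does not favour the adaptive or the standard arm.

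**Conclusion.** The contradiction is real and stands in the current text, but it is narrow. It lies between the unqualified sentence in 10.7.2 on one side and, on the other, Section 9.3 together with the eligibility review in the consent text and in 10.1 (the latter for routine TSCP visits). It bites most clearly for criteria 17 and 29 and partly for 14 and 18. Following 10.7.2 literally could pass an excludable participant to randomization; nothing in the protocol shows that this would happen often, and the number cannot be derived.

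This rests on two assumptions: that the initial-visit documentation contains the exam findings, and that the screening vitals include blood pressure. If blood pressure were treated as an exam finding, criterion 15 would join the list. The matter concerns participant safety and the make-up of the enrolled population. It deserves correction because it sits at the gate to randomization and is easy to remove, but it is no threat to the primary analysis.

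**What to change.** Reconcile 10.7.2 with Section 9.3 and the eligibility review by removing the blanket sentence or qualifying it. Possible wording: *The routine physical exam is not a separate eligibility test. Documented findings that bear on a Section 9.3 criterion are part of what the study medical provider reviews.* If the approved-drug sentence is kept, it should no longer read as the reason for disregarding exam findings.

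The cost is a short text amendment with the usual IRB approval. The exam is already done as part of clinical care, so no procedure is added, and no criterion or threshold changes. The possible downside is a few more screen failures, a number that the protocol gives no basis for estimating.

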### **Subject-Rated Non-Standardized Measures**

At each clinic visit, subjects will complete a number of assessments, some standardized and others non-standardized. All of these measures are completed by the subject as part of standard clinical practice. If the subject consents to research, the previously completed information will be recorded as Baseline measures. A Clinical Trials Assistant or other Key Personnel will review these as part of the screening process.

At the Initial visit to the TSCP or Duke CSC (baseline visit), the subject will complete the Smoking History questionnaire (Appendix 2). This non-standardized questionnaire provides information on the number of pack years, additional tobacco product use, and other drug use.

A subject's financial and insurance status is also assessed using the Financial Questions (Appendix 3). Cost of Smoking (Appendix 4) ascertains the amount the participant pays for cigarettes.

Medication Intolerance Questions (Appendix 5) determines if a participant's intolerance to a tobacco treatment medication or other contraindications to these medications (e.g. pregnancy) may exclude them from the study. Health and Surgery (Appendix 6) and Cancer Questions (Appendix 7) also measure if a participant should be excluded from the study for current symptomatic medical conditions. Race and ethnicity, are assessed in Demographics (Appendix 8).

### **10.7.3. Subject-Rated Standardized Measures**

A participant's alcohol use is assessed at Baseline using the AUDIT-C (Appendix 9). A score of 3 or higher (if female) or 4 or higher (if male) is considered a "positive" screen, and will require additional assessment from the study clinician to determine if the participant can be included in the study..

### **10.7.4. Subject-Rated Non-Standardized Measures to Be Collected at All Clinic Visits**

Thirty- and 7-day point prevalence are assessed in Recent Smoking (Appendix 11), as well as compliance with prescribed medications and reasons for non-compliance, if applicable.

A participant's employment status is assessed by Work Questions (Appendix 12); this measure also allows the study staff to calculate the amount of time spent during smoke breaks during the work day.

A participant's self-efficacy and motivation to stop smoking are assessed with Predictor Questions (Appendix 13).

### **10.7.5. Subject-Rated Standardized Measures to Be Collected at All Clinic Visits**

A number of standardized measures are collected at each clinic visit. All references are listed in each respective appendix. A participant's level of physical nicotine dependence is assessed using the FTND (Appendix 14).

A participant's current withdrawal symptoms from cigarettes is assessed in the MPSS-2 (Appendix 15). Depression is assessed using the PHQ-2 (Appendix 16), anxiety is assessed using the GAD-2 (Appendix 17) and stress is assessed using the PSS-4 (Appendix 18).

Finally, participants will be given a 7 day daily diary to complete prior to in-person study visits. This diary will ask about the number of cigarettes smoked per day and daily medication adherence. Participants will be asked to complete this prior to their visit. If they have not completed the diary prior to the visit, the RA will use the time-line follow-back approach to complete the 7 day diary with the participant. This form can be found in Appendix 20.

### **10.7.6. Subject-Rated Measures to Be Collected through Phone Assessment**

Participants will be followed up with by phone to answer questions about the following:

- Abstinence status
- Average number of cpd over the past 24 hours, 7 days, and 30 days
- Medications they are taking and side effects they are experiencing, if any
- Stress level
- Experience of urges
- Confidence in their ability to become tobacco free

These questions are also listed in Appendix 19

## **11 SAFETY MONITORING AND REPORTING**

The PI is responsible for the identification and documentation of adverse events and serious adverse events, as defined below. At each study visit, the PI or designee must assess, through non-suggestive inquiries of the subject or evaluation of study assessments, whether an AE or SAE has occurred.

The DCI Safety Surveillance is responsible for tracking and reporting SAEs to external and internal monitors. The DCI Safety Team will also manage any external safety reporting required by NIH and Pfizer. The contact for this is [name], [contact].

### **11.1 Adverse Events**

An adverse event (AE) is any untoward medical occurrence in a subject receiving study therapy and which does not necessarily have a causal relationship with this treatment. For this protocol, the definition of AE also includes worsening of any pre-existing medical condition. An AE can therefore be any unfavorable and unintended or worsening sign (including an abnormal laboratory finding), symptom, or disease temporally associated with the use of study therapy, whether or not related to use of the study therapy. Abnormal laboratory findings without clinical significance (based on the PI's judgment)

should not be recorded as AEs. But laboratory value changes that require therapy or adjustment in prior therapy are considered adverse events.

From the time the subject signs the informed consent form through the End of Study visit (as defined in Section 10.3), all AEs must be recorded in the subject medical record and adverse events case report form. The investigator will follow all reportable events until resolution, a return to baseline condition or stabilization.

AEs will be assessed according to the CTCAE version 4.0. If CTCAE grading does not exist for an AE, the severity of the AE will be graded as mild (1), moderate (2), severe (3), life-threatening (4), or fatal (5).

Attribution of AEs will be indicated as follows:

- Definite: The AE is clearly related to the study therapy
- Probably: The AE is likely related to the study therapy
- Possible: The AE may be related to the study therapy
- Unlikely: The AE is doubtfully related to the study therapy
- Unrelated: The AE is clearly NOT related to the study therapy

#### **11.1.1. AEs of Special Interest**

There are not AEs of particular concern or interest in this study because all medications used are FDA approved for smoking cessation.

#### **11.1.2. Reporting of AEs**

During each annual IRB review of the protocol, a list of all AEs will be provided to the IRB for review. This report includes whether the AE was likely related to study procedures, whether it impacted subject participation, whether the AE was resolved, and any other action taken.

### **11.2 Serious Adverse Events**

An AE is considered “serious” if in the opinion of the investigator it is one of the following outcomes:

- Fatal
- Life-threatening
- Constitutes a congenital anomaly or birth defect
- A medically significant condition (defined as an event that compromises subject safety or may require medical or surgical intervention to prevent one of the three outcomes above).
- Requires inpatient hospitalization or prolongation of existing hospitalization
- Results in persistent or significant incapacity or substantial disruption to conduct normal life functions.

All SAEs must be followed until resolution, a return to baseline condition, stabilization, or 30 days after the subject’s last dose of study drug whichever occurs first. Any SAEs that are ongoing at the time the clinical database is closed will be reported to the supporting company as unresolved.

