### 10.4 Follow-up Period

Following the End of Treatment, participants will receive two follow-up phone assessments (detailed further in section 10.7). These phone assessments will occur at 26-weeks post-TQD and 52-weeks post-TQD. If participants are not currently abstinent from tobacco at the End of Treatment, a referral to clinical resources within the TSCP will be offered.

**Follow up Study Assessment Visits:** At each assessment visit, there will be a standardized evaluation. The screening will be provided through the Duke Smoking Cessation Program for clinical purposes. Later assessments (Enrollment, Medication Response, 2- and 12-week post quit) will be provided by the CTA. During these visits there will be multiple self-report assessments (see below) as well as CO testing. Finally each participant will receive a total of 10 phone calls out to 1 year post quit attempt. Biochemically confirmed 30-day continuous abstinence at twelve weeks post-Target Quit Day is the primary endpoint to determine abstinence. Other endpoints, including biochemically confirmed 7-day point prevalent abstinence at two and twelve weeks post-TQD and self-reported abstinence rates via phone-based assessment up to 52-week post-TQD, will also assess abstinence as secondary measures.

**Phone-based Assessment Time Table:** The phone assessments function to collect data on study participants but also to check on difficulties with medications, medication side effects and to remind participants of upcoming visits. The timing is as follows:

|    |                                            |
|----|--------------------------------------------|
| 1  | 1 day after the Enrollment Visit           |
| 2  | 1 day before the Medication Response Visit |
| 3  | 1 day pre-TQD                              |
| 4  | 1 day post-TQD                             |
| 5  | 1-week post-TQD visit                      |
| 6  | 1 day before the 2-week post-TQD visit     |
| 7  | 6-week post-TQD time point                 |
| 8  | 1 day before the 12 week post-TQD visit    |
| 9  | 26 week post-TQD time point                |
| 10 | 52 week post-TQD time point                |

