### 10.5 End of Study

Study participation will end with each participant after the 52-week post TQD phone assessment. If participants cannot be reached by phone, they will be contacted by additional means including email or other contact methods listed. If they are still not able to be contacted, they will be listed as "lost to follow up" for purposes of analysis of results (see management of missing data in analysis). If participants are not abstinent from tobacco at the End of Treatment, a referral to clinical resources within the TSCP will be offered. After all participants have completed the study, study data collection period will be considered over and the team will begin analysis of results. Analysis may continue for up to 5 years. This is necessary because of multiple sub-analyses that may be performed on the large quantity of data generated from this trial. After this 5-year period, it is expected that the trial will lock the data.

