#### **11.2.1. Reporting of SAEs**

Life-threatening (grade 4 or 5) SAEs, deaths, and unknown reactions or unexpected events that occur in the course of any patient’s treatment of study (from the time of consent) or within 30 days following cessation of treatment are reportable. All SAE’s will be reported to the IRB. The initial report for each SAE or death should include at minimum the following information:

- Protocol # and title
- Patient initials, study identification number, sex, age
- Date the event occurred
- Description of SAE
- Description of patient’s condition
- Indication whether the patient remains of study
- Causality or causal relationship

De-identified source documentation (i.e. discharge notes) must be sent with the SAE Report Form. Follow-up information including severity, action taken, concomitant medications, and outcome should be communicated to Duke as soon as possible using the same forms mentioned above.

As soon as an investigator becomes aware of an AE that meets the definition of serious:

- DCI Safety Surveillance must be notified and they will submit to Pfizer of designee within 24 hours of Investigator's awareness, even if it is not felt to be drug related. Report to Pfizer U.S. Clinical Trial Department ([contact])
- The investigator agrees to provide supplementary information requested by Pfizer Drug Safety personnel or designee.

SAEs will be reported by the P.I. in an expedited manner to the Duke University Health System (DUHS) Institutional Review Board (IRB) office, NIDA, and FDA.

SAEs will be reported to the DUHS IRB using the following timelines:

- 24 hours – for an unanticipated study-related death
- 1 week (5 business days) – for an unanticipated problem that is a serious adverse event
- 2 weeks (10 business days) – for an unanticipated problem that does not meet the criteria of a serious adverse event

SAEs will be reported to the NIDA Serious Adverse Event Tracking and Reporting System (SAETRS) within 72 hours. The NIDA Program Official will be kept apprised of IRB actions related to SAEs and any plan to modify the protocol as a result of IRB recommendation will be subject to NIDA approval.

In accordance with applicable regulations, investigators will submit the SAE report to their local IRB according to local IRB institutional guidelines.

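### Sections 11.1 and 11.2 give different rules for when SAE follow-up ends, AE recording ends at a visit defined by the wrong section, and treatment completers have no scheduled contact in the 30-day reporting window

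*Protocol*

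**What the plan says.** **Length of follow-up.** Section 11.1: "The investigator will follow all reportable events until resolution, a return to baseline condition or stabilization". It sets no limit in days. Section 11.2 uses the same three end points for SAEs and adds a fourth, 30 days after the "last dose of study drug whichever occurs first". The next sentence of 11.2 deals with "Any SAEs that are ongoing at the time the clinical database is closed" and has them reported as unresolved.

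**End of AE recording.** Section 11.1 runs from consent "through the End of Study visit (as defined in Section 10.3), all AEs must be recorded". Section 10.3 is headed End of Treatment and describes the 12-week post-quit visit. End of Study is section 10.5: "Study participation will end with each participant after the 52-week post TQD phone assessment". The Schedule of Activities marks AE assessment at the follow-up calls and at the 52-week call.

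**Reporting window and contacts.** Under section 11.2.1, life-threatening SAEs, deaths and unknown or unexpected events arising on treatment or "within 30 days following cessation of treatment are reportable". Section 10.4 gives two contacts after end of treatment: "These phone assessments will occur at 26-weeks post-TQD and 52-weeks post-TQD".

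**Pregnancy.** Section 11.2 lists among the serious outcomes: "Constitutes a congenital anomaly or birth defect". Section 11.4 makes pregnancy reportable and gives no time limit.

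**The concern.** Sections 11.1 and 11.2 can give staff opposite instructions for the same serious event. Someone who follows 11.2 may close an event that is still active; someone who follows 11.1 keeps it open. The 11.2 clock starts at the last dose and not at onset, so the later an event begins, the less follow-up it is owed.

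The section number in 11.1, taken literally, stops AE recording at the visit where drug is discontinued. That would leave nothing recorded in the 30 days that 11.2.1 treats as reportable.

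At stake are the outcomes of serious events that begin late or last long, and the completeness of off-drug safety data. The primary abstinence endpoint is not affected.

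**Working it through.** The protocol gives no calculated figure to reproduce here. The check is date arithmetic in days from TQD, followed by a comparison of the passages.

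**Inputs**
- Treatment runs from 4 weeks before TQD to 12 weeks after (section 3.5): day -28 to day 12 × 7 = 84. The dispensed supply in section 8.5 agrees: 3 + 4 + 9 = 16 weeks, and -28 + 16 × 7 = 84.
- Visits fall on days -28, -14, 14 and 84. Calls fall on days -27, -15, -1, 1, 7, 13, 42, 83, 182 and 364 (section 10.4).
- The SAE limit (11.2) and the reporting window (11.2.1) are both 30 days off drug.

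**Follow-up rule**
- For a completer the limit falls on day 84 + 30 = 114.
- An SAE with onset 29 days after the last dose begins on day 84 + 29 = 113. Under 11.2 it is owed 114 - 113 = 1 day. Under 11.1 it is followed until one of the three clinical end points is reached.
- Section 10.5 ends data collection only after all participants have finished. If the database closes no earlier than that, closure comes at least 364 - 114 = 250 days after a completer's limit. To report an SAE as ongoing at that point, someone must still know its status, and the 30-day stop does not require anyone to.

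**End of AE recording**
- By section number (10.3): week 12. By name (10.5 and the Schedule): week 52.
- Difference: 52 - 12 = 40 weeks, or 364 - 84 = 280 days.

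**Contacts in the 30-day window**
- Completers: there are no scheduled contacts on days 85 to 114. The next is day 182, which is 182 - 84 = 98 days after the last dose and 182 - 114 = 68 days after the window closes.
- Early stoppers: going through each possible last-dose day before day 84, a scheduled contact falls in the following 30 days except for last doses on days 42 to 52.
- Content of the week-26 call (Appendix 19): the side-effect item asks about effects being experienced now. The items added for weeks 26 and 52 concern cessation medication and smoking. The others cover smoking, urges, withdrawal, motivation and confidence. A hospital stay on, say, day 100 that was over by day 182 is not elicited by any printed item.

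**Pregnancy**
- Assume about 38 weeks (266 days) from conception to birth. Conception on day -28 gives birth on day 238, and conception on day 84 gives day 350. Both fall after day 114.
- The result does not depend on the 38 weeks. Conception on treatment precedes the last dose by at most 84 + 28 = 112 days, so any interval to birth longer than 112 + 30 = 142 days ends outside the window.

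**The case against.** **The section number is a slip.** Section 11.1 names the End of Study visit, and the Schedule has an End of Study column with AE assessment marked. This stands: name and Schedule together point to 10.5, and the 40 weeks arise only if the number overrides both. The number still needs correcting, because it leads to a real section with a different end point.

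**The database-closure sentence shows that outcomes are not lost.** Partly right. Long-lasting SAEs are to be carried as unresolved, so a reader who infers that the protocol discards their outcomes goes too far. But the sentence fits the 30-day stop only if status is frozen at that limit, which the text does not say.

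**Reportable is undefined in 11.1.** True, so it cannot be asserted that every non-serious event is followed longer than a serious one. The conflict survives the narrow reading, because 11.2.1 applies the word to life-threatening SAEs and deaths.

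**A reporting window does not require a contact inside it.** Correct, so this part is a gap and not a contradiction. It concerns scheduled contacts for completers. Section 7.1.2 asks participants to phone in side effects, section 10.6.2 adds a Premature Withdrawal Visit, and the Schedule requires AE assessment at the week-26 call, where a caller may ask more than Appendix 19 prints.

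**Inferences to avoid.** A reader might set the 68 days against the 24-hour reporting rule in 11.2.1. That clock starts when the investigator becomes aware, so late discovery is not a breach. A reader might also expect reporting to diverge between sites, but section 11.8 says that the study does not use multiple clinical sites. Nor is pregnancy unaddressed: 11.4 makes it reportable. What is missing is how the 11.2 limit applies to its outcome.

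**Conclusion.** The point holds as two text errors and one coverage gap.

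- Sections 11.1 and 11.2 disagree on when SAE follow-up ends, and 11.2 does not fit its own next sentence. At the extreme, an event that 11.2.1 makes reportable is owed one day of follow-up.
- The cross-reference in 11.1 leads to week 12 where the name and the Schedule indicate week 52, a difference of 40 weeks.
- For completers, the 30-day window passes without a scheduled contact, and the week-26 script as printed would not retrieve a serious event that has already resolved.

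This assumes that the last dose is on day 84, that contacts occur on their nominal days, and that Appendix 19 is the full call script. The documents do not show which follow-up rule was intended, and no count of affected events can be derived from them. The matter is worth correcting because the off-drug safety record depends on it and the change is small.

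**What to change.** 1. Reconcile 11.1 and 11.2 into one rule for SAE follow-up that also fits the sentence on database closure. State the 30-day onset window of 11.2.1 separately, so that onset and duration of follow-up are not confused. Which follow-up rule applies is for the sponsor and investigator to decide.
2. In 11.1, correct the reference from 10.3 to 10.5, so that the end of AE recording matches the Schedule of Activities.
3. Add one retrospective question to the existing week-26 call: any hospital stay, emergency visit or other serious event since the 12-week visit (or the last contact, if that visit was missed), with the date of onset. This retrieves events from days 85 to 114; it does not place a contact in the window.
4. State how the SAE time limit applies to pregnancies reported under 11.4. Include participants who have been withdrawn: pregnancy is a listed reason for withdrawal in 10.6.1, and they may not receive the week-26 and week-52 calls.

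Cost: a few sentences in section 11, one item on a call already scheduled, and possibly some SAEs kept open longer, depending on the rule chosen.
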